### Data collection

A schedule of data collection is shown in the SPIRIT diagram in Fig. 2 [64]. Inter-rater training was conducted for observer-rated measures prior to recruitment. Inter-rater reliability between researchers for the MADRS was high (ICC = .995 (*p* < .001), 95% CI .987 to .999).

**Fig. 2 Fig2:**
[figure not shown]
Standard Protocol Items: Recommendation for Interventional Trials (SPIRIT) diagram of assessments at enrolment, allocation, 3-weekly sessions, post-intervention, 3-month and 6-month time points. ^a^Administered in the intervention group only. ^b^Rated pre-session and post-session. *BDI-II* Beck Depression Inventory-II, *CSQ* Client Satisfaction Questionnaire, *CSRI* Client Services Receipt Inventory, *DMS* Dimensional Mood Scale, *GPSES* General Perceived Self-efficacy Scale, *IIM* Interest in Music Scale [95], *LSP* Life Skills Profile, *MADRS* Montgomery-Åsberg Depression Rating Scale, *MANSA* Manchester Short Quality of Life Scale, *RSES* Rosenberg Self-esteem Scale, *RSS* Relationship Satisfaction Scale, *WSAS* Work and Social Adjustment Scale

Baseline assessments will occur as soon as possible after informed consent is obtained. Follow-up visits will be arranged in the week following the end of the intervention, and at 3 and 6 months after the intervention end. Participants in the intervention arm will each receive a payment of £10 to contribute towards travel costs and participants in the wait-list control group will each receive £15 in the form of shopping vouchers. Participants will be eligible to receive assistance with the cost of transport to and from therapy sessions if they currently do not receive such help.

Researchers conducting blind follow-up assessments will enter the data onto paper case report forms designed for each assessment. These will be transferred into an electronic database and double-entered. Limits are set on data values to be entered to ensure only valid entries are permitted.

### Nested process evaluation

We will conduct a process evaluation with the following aims:To understand exactly how the intervention was delivered in practice (treatment fidelity analysis)Describe processes of attendance and hypothesised process factors of self-reported depression, mood and group relationships from week to weekUnderstand subjective experiences and attributions for change of the intervention from the perspective of patients, music therapists and referring staffCompare reported quantitative and qualitative processes against the proposed logic model and to revise accordingly

The process evaluation will employ an embedded mixed methods design and will consist of data collection of video data of the intervention itself, client self-reported measures (weekly quantitative process measures of mood pre-session and post-session (DMS [86]), group relationships pre-session and post-session (RSS) [87]) and qualitative end interviews 1 month post-intervention. The interview is optional for service users but we aim to conduct a minimum of 12 interviews.

Quantitative analysis will provide a descriptive analysis of the course of weekly process measures. We will descriptively explore whether there are any differences between compliant and non-compliant attenders, responders and non-responders and whether any socio-demographic and clinical characteristics are associated with outcomes.

Qualitative evaluation will comprise end-of-study interviews with 12 participants, their referring staff and music therapists. Whilst interviews will have a component to focus upon experiences of the research and views on the design, a second part will ask for views on the experience of the group music therapy itself. These questions are based upon a pre-existing semi-structured interview (Client Change Interview [88, 89]) to elicit clients’ views of and attributions for change. We have adapted this interview for music therapists and referring clinicians to also reflect upon possible observed changes in the participants who they have worked with and their views of the intervention.

Interviews will be transcribed and imported into NVivo qualitative analysis software and read a number of times by members of the research team. Members will individually code 25% of the interviews and then meet to decide upon a preliminary thematic frame. As interviews will be asking about individual experiences, coding will take a phenomenological perspective and seek to retain the essence of individual narratives. The team will continue to code and meet regularly to discuss the adequacy of the frame in reflecting individual experiences. Once a final thematic frame is agreed, we will then explore relationships between the themes identified in the data and quantitative findings. Quantitative and qualitative data will be compared against the hypothesised logic model for our intervention. We will then refine and revise the logic model based upon these findings.

### Sample size

This study aims to assess the feasibility of recruitment processes including the number of eligible participants and participation/retention rates. Papers considering sample size for feasibility and pilot studies suggest the inclusion of upwards of 24–50 participants [59, 90, 91]. The present study aims to recruit 30 patients to participate in three groups of 10 patients each. In order to obtain sufficient data on the intervention, randomisation will be imbalanced so that 20 are randomised to the treatment arm and 10 to the wait-list control group.

Studies of wider psychosocial and psychotherapeutic interventions for chronic depression show participation rates in the range of 25–33% of eligible patients consenting to participate in the study [92–94]. With a sample size of 30, we will be able to estimate a participation rate of 25% to within a 95% confidence interval of +/-15%. Assuming that one fifth of patients accessing primary care for depression will have developed chronic depression, we estimate approximately 1300 patients within primary care will be eligible for this study. We estimate each practice will have around 100 patients with depression, of which around 20 will have enduring symptoms. Within the secondary care sites in which we plan to recruit, there are currently around 1960 patients with a diagnosis of depression. Assuming that one fifth will have developed chronic depression [1], we estimate approximately 392 patients within secondary care will be eligible for this study. Based on a participation rate of 25%, we plan to approach 128 patients with the aim of recruiting 4 per week, over 8 weeks.

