### Participant identification and recruitment process

Participant identification, recruitment and follow-up procedures are shown in Fig. 1. Recruitment will commence 8 weeks before the first scheduled music therapy group. Patient identification will be made by a member of the patient’s existing clinical care team in the following ways:Primary care PICs: GP surgeries. All adults on record as meeting the inclusion criteria will be identified by an administrator working within the service. The researcher will provide a letter of invitation which will be sent out with an information sheet. Those expressing interest will be invited to speak with the researcher for further information.Talking therapies (IAPT) service and CMHTs. Patients meeting the inclusion criteria will be informed of the study and provided with an information sheet by the healthcare professional overseeing their care. Assent will be gained for the professional to put the patient in touch with the researcher. Where possible, a researcher will be based on site to speak with patients to minimise further additional visits.

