### Outcome measures and endpoints

Our primary interest is in the feasibility of the trial design and intervention. A summary of the main feasibility outcomes, success criteria and timing is shown in Table 1. Proposed clinical outcomes are:

**Table 1 Tab1:** Methods and timing for assessing, recording and analysing outcome parameters

Outcome	Method	Success criteria				Timing
		Stop	Continue, modify protocol	Continue without modification but monitor closely	Continue without modifications	
Acceptability of methodology	Recruitment and retention rates as below					End of recruitment (week 8)
	Compliance	Mean attendance <10 sessions	Mean attendance <14 sessions	Mean attendance 14 sessions	Mean attendance 14+ sessions	End of intervention (week 22)
	End interviews	Unfavourable views, serious concerns	Unfavourable views, suggestions for modification	Favourable views, suggestions for modification	Favourable views, no concerns	1 month post-intervention (week 26)
Feasibility of recruitment processes	Screening rates	Identify <50 potentially eligible subjects	Identify <100 potentially eligible subjects	Identify 100–128 potentially eligible subjects	Identify >128 potentially eligible subjects	End of recruitment
	Recruitment rates	Recruit <50% of sample size	N <25 in 8wks, <5% per week	*N* = 25–30 in 8wks, <13% per week	*N* = 30 in 8wks, 13% per week or greater	End of recruitment
	Participation rates	Participation rate <5%	Participation rate 5–15%	Participation rate 15–25%	Participation rate 25% or greater	6 months post-intervention
	Retention rates	Attrition >75%	Attrition 50–75%	Attrition 30 − 50%	Attrition <30%	6 months post-intervention
	End interviews	N/A	Major suggestions to improve recruitment processes	Minor suggestions to improve recruitment processes	No suggestions to improve expressed	1 month post-intervention (week 26)
Identify number of eligible participants, participant rates and retention rates	Number identified by HCPs	<50 identified	50–100 identified	100–128 identified	>128 potentially eligible identified	End of recruitment
	Number expressing interest	<30 express interest	30–40 express interest	40–60 express interest	>60 express interest	End of recruitment
	Number providing consent	<15 provide consent	15–25 provide consent	25–30 provide consent	30 provide consent	End of recruitment post-intervention, 3 and 6 months post-intervention
	Number lost to follow up	Attrition >75%	Attrition 50–75%	Attrition 30–50%	Attrition <30%	

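### The ±15-point precision for the participation rate is computed on the 30 recruited, who are its numerator; on the patients approached it is about ±7.5 points, and Table 1 leaves that denominator undefined

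*Protocol article*

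**What the plan says.** The Sample size section of the protocol article introduces the participation rate through other psychosocial trials in chronic depression, which had "participation rates in the range of 25–33% of eligible patients consenting to participate in the study". It then gives its own precision: "With a sample size of 30", "we will be able to estimate a participation rate of 25% to within a 95% confidence interval of +/-15" percentage points. Later in the same paragraph, again at 25%, comes the recruitment plan: "we plan to approach 128 patients with the aim of recruiting 4 per week, over 8 weeks".

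The target is 30 patients, and under Randomisation allocation waits until all 30 are recruited.

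Table 1 (Outcome measures and endpoints) sets progression bands. The top bands are "Identify >128 potentially eligible subjects" for screening, 30 consents for consent, and "Participation rate 25% or greater" for participation. The participation row names no denominator. The next band down, 15–25%, lets the trial go on unmodified under closer watch; 5–15% calls for a modified protocol.

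Under Participant identification and recruitment process, the GP route is open-ended: "All adults on record as meeting the inclusion criteria will be identified by an administrator working within the service". The criteria are confirmed only for interested patients who meet the research team.

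**The concern.** All 30 recruited patients have consented, so within them the participation rate is 100% by construction and nothing is left to estimate. A 25% rate can be estimated only among the people who were asked. The printed error bar therefore belongs to a different quantity from the one it names. It matters because this is the only planned precision in the article, and because participation is one of the study's stated aims and carries its own progression band.

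The same uncertainty about the denominator reaches Table 1. Consents stop at 30, while the number identified or approached does not. If the rate is taken over that open-ended number, the band reached depends partly on how many invitations go out, not only on how willing patients are to take part.

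**Working it through.** **Inputs.** Participation rate 25%, 95% confidence, stated half-width 15 points, n = 30, 128 to be approached, 4 per week for 8 weeks (all from Sample size). Top bands: more than 128 identified, 30 consents, participation of at least 25% (Table 1).

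**Step 1: reproduce the stated figure.** Half-width = 1.96 × √(p(1 − p)/n), with p = 0.25.

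- n = 30: 1.96 × √(0.1875/30) = 0.155, or 15.5 points (Wilson interval: 14.9 points).
- n = 32: 1.96 × √(0.1875/32) = 0.150, or 15.0 points.
- Solving for exactly 15 points: n = 1.96² × 0.1875/0.15² ≈ 32.

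The stated figure therefore comes from the recruited number used as the binomial n.

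**Step 2: use the patients approached.**

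| Eligible patients approached | Consents at 25% | 95% half-width | Interval |
|---|---|---|---|
| 120 | 30 | 7.7 points | 17.3% to 32.7% |
| 128 | 32 | 7.5 points | 17.5% to 32.5% |

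The Wilson interval for 32/128 is 18.3% to 33.2%, so the choice of method makes little difference. The ratio of stated to recomputed half-width is 15/7.5 = 2.

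Against Table 1, ±15 points around 25% runs from 10% to 40% and touches three participation bands. ±7.5 points touches two.

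**Step 3: where 128 comes from.** 4 × 8 = 32 recruits, and 32/0.25 = 128. For the 30 actually taken, 30/0.25 = 120.

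**Step 4: the top bands, if participation is consents over patients identified or approached.**

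- 30/128 = 23.4%, below 25%.
- 30/129 = 23.3%, below 25%. (129 is the smallest number that meets the top screening band.)
- 30/120 = 25.0%, so 120 is the largest denominator at which 30 consents reach the top band.
- 30/200 = 15.0%, so beyond 200 the rate falls into the band that calls for a modified protocol. At the article's estimate of around 20 patients with enduring symptoms per practice, 200 is 200/20 = 10 practices.

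**The case against.** The best defence is that the error is harmless. It claims less precision than the study would have, and 30 does not rest on it alone: the same section cites sample-size guidance for pilot studies and plans three groups of ten. That stands. A reader might infer that 30 is too small or that the sample size is unsupported, but the documents do not show this.

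A reader might also infer that the three top bands can never be met together. That goes too far. The screening row counts potentially eligible patients, the Sample size section speaks of eligible patients and of patients approached, and the participation row is silent. If 9 of 129 identified proved ineligible or were not approached, 30/120 would be 25% and all three bands would hold. The conflict exists only if the denominator is everyone identified, or the full 128 approached.

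Nor do the documents support the prospect of a fully recruited trial landing in the stop band. That needs more than 30/0.05 = 600 in the denominator, against 128 planned. Dividing 30 by the whole estimated pool of 1300 + 392 = 1692 gives 1.8%, but nobody plans to approach that pool.

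Planning for 32 is not itself a mistake: 30/8 = 3.75 per week, rounded up to 4. It matters only because 128 was carried into Table 1 beside a consent figure of 30. The absence of a precision for retention is a detail that an article may leave to the full protocol, and it is not part of this point.

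**Conclusion.** The precision statement is wrong as printed. For the rate it names, at the planned 128 approached, the half-width is about 7.5 points, half the stated value. The statement does not support the choice of 30, and correcting it does not undermine that choice. This part rests only on the article's own description of participation and on treating the patients approached as a simple binomial sample.

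The Table 1 point is conditional. If participation is taken over patients identified or approached, a fully recruited trial that approached exactly 128 scores 23.4% and falls one band, with the trial still continuing unmodified. It would fall a further band only if more than 200 were approached. The article sets no number of practices, so that is possible but not planned. The underlying fault is an undefined denominator beside a numerator that stops at 30. The correction is modest but should be made, because the progression decision will be read from these bands.

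**What to change.** 1. In Sample size, replace the precision sentence with one stating that, among about 120 to 128 eligible patients approached, a participation rate of 25% would be estimated to within about ±7.5 points (95% confidence). Do not tie this figure to the 30.
2. In the participation row of Table 1, define the rate as consents divided by eligible patients approached up to the 30th consent. Identifying more patients, or closing recruitment once 30 places are filled, then no longer lowers the band mechanically. Because GP invitations may go out in batches, the definition should also say how patients who have been invited but have not yet replied at the 30th consent are counted.

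With that definition the number identified and the participation denominator are separate quantities, so the screening band of more than 128 can stay as it is. The cost is one sentence and one table cell. The sample size, allocation and analysis are unchanged.

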### Statistical analysis

#### Feasibility

As this is a feasibility study, the main statistical reporting will comprise descriptive statistics and calculation of effect sizes. We will assess:• Acceptability of methodology to professionals and patients through interviews via recruitment rates, compliance, end interviews      • Feasibility of recruitment processes• Deviation around specific post-intervention, and 3-month and 6 month post-intervention follow-up assessment dates for actual data collection• Number of eligible participants, participation rates and retention rates• Researcher time and costs per participant• Appropriateness of outcome measures

Descriptive analyses will establish recruitment and drop-out rates and the distribution of baseline characteristics and all outcomes post-intervention, and 3 months and 6 months post-intervention. The research team will reflect upon the representativeness of the demographics in terms of the general population of patients that could potentially be useful in assessing the intervention.

Recruitment and drop-out rates will be monitored on a monthly basis allowing for examination and reporting of patterns and whether there are any obvious trends. This may inform the choice of the primary outcome for a full-scale trial allowing for drop-outs in a sample-size calculation.

#### Clinical outcomes

This study will employ intention-to-treat analysis. Data from all subjects will be included in the analysis as randomised. Adverse events will be reported by sub-groups of those who were currently receiving the intervention and those who were not.

We will first calculate a mean value of the outcome for each unit and present them with confidence intervals. Outcomes will be compared between intervention and control groups using linear regression models, adjusting for the baseline score of the given outcome. The confidence limits of each treatment effect and knowledge of the clinically important difference (where this is available) will be used to determine whether clinically important differences are ruled out by these confidence limits. The intra-cluster correlation coefficient will be calculated. Due to the small sample size, this estimate is likely to be imprecise, therefore we will also use estimates in the literature from similar studies for comparison to inform the design of any future studies. We will descriptively explore in sub-group analyses whether there are any differences between compliant and non-compliant attenders, responders and non-responders and whether any socio-demographic and clinical characteristics are associated with outcomes. As a preliminary economic evaluation, we will calculate the cost of delivery of music therapy and cost of services received by both groups using the CSRI [83]. This will be descriptive only to provide an estimate for future studies.

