### Intervention

The intervention has been described in full in a manual developed for the purposes of this study and has been informed by existing manuals for group songwriting [44], individual psychodynamic music therapy for depression [30, 47] and principles of resource-oriented music therapy [48]. The intervention was developed through focus group discussions with music therapists, psychologists and service users with a diagnosis of depression and was finalised in team discussions with music therapists and Heads of Arts Therapies involved in the study. The Template for Intervention Description and Replication [63] and Standard Protocol Items: Recommendations for Interventional Trials (SPIRIT) [64] checklists are attached as Additional files 1 and 2. The intervention manual and full study protocol are available on request from the authors.

Group music therapy will be provided three times per week over 14 weeks by two HCPC-registered music therapists. Each session will last 90 minutes and will comprise warm-up activities moving to sharing of pre-known songs and improvisation. Therapists will move from improvisation into songwriting, which will then be the main focus for the remainder of the session. Opportunities will be offered after each activity for verbal reflection. The last 15 minutes will be dedicated to reviewing the session and may include playing through a final piece of music.

The intervention will be provided in a community centre within the locality of Newham. The community centre is a non-NHS site and offers facilities for additional social contact such as a café and wider non-medical community groups. Music therapists will receive weekly clinical supervision from the chief investigator.

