### Criteria for discontinuation

Participants will be withdrawn from the intervention if the participant becomes too unwell to continue due to loss of capacity to consent to group attendance, if the patient has a level of risk assessed by the clinical team to require hospitalisation or if music therapists and the clinical team determine that the patient’s current mental state, behaviour or risk to self or others requires discontinuation of the intervention. Reasons for withdrawal will be documented as part of feasibility measures.

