### Randomisation

Randomisation will occur once all 30 participants have been recruited and baseline measures have been completed. In order to obtain sufficient data on the intervention, we will utilise simple block randomisation with unbalanced allocation so that 20 participants receive the intervention and 10 are allocated to the wait-list control group. A researcher independent of the study team will perform the randomisation using the Experimental Design Generator and Randomiser (EDGAR-II) [65] and inform the music therapists and unblinded member of the study team of the allocation by email. The music therapists will then inform participants of their allocation and provide additional support if required.

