### Trial governance, monitoring and auditing

The Trial Management Group (TMG) consists of the chief investigator, study team and co-investigators and will provide overall management of the study including set-up, training, recruitment, promotion of the study and interpretation of results. Given the small and exploratory nature of the trial, no interim analysis is planned. Further to consultation with the study sponsor, the team considers that the nature of the intervention does not pose a significant risk to the study participants, and therefore we will not use a data monitoring committee. An Independent Advisory Panel (IAP) consisting of two independent members will monitor the conduct of the trial and meet four times over the course of the study to discuss research progress according to defined milestones, emerging difficulties and dissemination of results.

The chief investigator in liaison with the sponsor and the IAP has ultimate authority to halt the study or withdraw individual participants should concerns arise during the study. Adverse events will be monitored and recorded throughout. All serious adverse events will be reported to the sponsor and reported to the REC if assessed to be serious, related to the study and unexpected. Adherence to the protocol and any subsequent amendments will be supervised by the sponsor. Access to data will be granted to authorised representatives from the sponsor, host institution and the regulatory authorities, to permit trial-related monitoring, audits and inspections.

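### The only stated grouping for adverse events is current receipt of therapy, which pools the intervention arm's post-course and post-withdrawal events with those of the wait-list arm

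*Protocol article*

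**What the plan says.** Under Clinical outcomes, the protocol article adopts intention-to-treat and states: "Data from all subjects will be included in the analysis as randomised". The next sentence gives the rule for harms: "Adverse events will be reported by sub-groups of those who were currently receiving the intervention and those who were not". The article states no other grouping for adverse events.

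Four other sections determine what that rule does in practice:

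- Randomisation: "20 participants receive the intervention and 10 are allocated to the wait-list control group".
- Intervention: "Group music therapy will be provided three times per week over 14 weeks by two HCPC-registered music therapists".
- Data collection: "Follow-up visits will be arranged in the week following the end of the intervention, and at 3 and 6 months after the intervention end". Trial governance, monitoring and auditing adds: "Adverse events will be monitored and recorded throughout".
- Criteria for discontinuation: "Participants will be withdrawn from the intervention if the participant becomes too unwell to continue" through loss of capacity, and also "if the patient has a level of risk assessed by the clinical team to require hospitalisation".

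The section on the wait-list control makes that arm eligible for group music therapy only after its 6-month follow-up is complete.

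**The concern.** Current receipt changes over time within a patient, and in part it changes because of how the patient is doing. Someone in the intervention arm counts as receiving during the course and as not receiving once it ends. Someone withdrawn early for deterioration or risk changes category at that moment. Any later event in either patient is counted beside the events of people who were never offered the therapy during the study.

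The category meant as the comparison is therefore a mixture of the two arms. Events that arise after a participant leaves the group, or after a thrice-weekly group stops, are the ones that end up in it. The article says the results are to inform a larger trial, and that trial's planners would want to see harms by arm.

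The wait-list design does not force this choice. Controls start therapy only after the last study assessment, so an uncontaminated comparison by arm is available for the whole follow-up.

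**Working it through.** The article gives no figure for adverse events, so there is none to reproduce. The check is person-time arithmetic on the trial's own schedule.

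**Inputs from the article:** 20 intervention and 10 wait-list participants; a 14-week course; follow-up to 6 months after the course; events recorded throughout.

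**Assumptions:** 6 months is taken as 26 weeks (24 as a check); no loss to follow-up; wait-list time is counted over the same calendar period.

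**Step 1. Person-weeks under the stated rule (26 weeks).**

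- Receiving: 20 × 14 = 280.
- Not receiving, intervention arm after the course: 20 × 26 = 520.
- Not receiving, wait-list arm: 10 × (14 + 26) = 400.
- Not receiving, total: 520 + 400 = 920.
- Intervention-arm share of the not-receiving category: 520/920 = 57%.
- Share of the intervention arm's own time that falls there: 520/800 = 65%.

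With 24 weeks instead, the shares are 480/860 = 56% and 480/760 = 63%.

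**Step 2. Early withdrawal from therapy (assumed: a share stops at week 7 and stays in follow-up; 26 weeks).**

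- 30% stop: receiving = 14 × 14 + 6 × 7 = 238; intervention-arm time off therapy = 800 − 238 = 562; share of the not-receiving category = 562/962 = 58%; share of the arm's own time = 562/800 = 70%.
- 50% stop: receiving = 10 × 14 + 10 × 7 = 210; off therapy = 590; shares 590/990 = 60% and 590/800 = 74%.

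The dilution thus comes mainly from the end of the course. Withdrawal adds little person-time, but the time it adds belongs to patients selected for deterioration.

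**Step 3. What a reader of the table would see.** Rates are assumed for illustration, per 100 person-weeks, with the wait-list at 5 and no early withdrawal.

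| Intervention-arm rate: during / after course | Rate by arm (intervention) | Ratio by arm | Rate in not-receiving category | Ratio, receiving vs not |
|---|---|---|---|---|
| 10 / 10 (excess throughout) | (28 + 52)/800 = 10.0 | 2.0 | (52 + 20)/920 = 7.8 | 10/7.8 = 1.28 |
| 5 / 10 (excess only after) | (14 + 52)/800 = 8.25 | 1.65 | (52 + 20)/920 = 7.8 | 5/7.8 = 0.64 |
| 10 / 5 (excess only during) | (28 + 26)/800 = 6.75 | 1.35 | (26 + 20)/920 = 5.0 | 10/5 = 2.0 |

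Numerators are expected events (for example 280 × 0.10 = 28, 520 × 0.10 = 52, 400 × 0.05 = 20), and rates are shown per 100 person-weeks. In the second row the therapy would look protective although its arm carries the excess. In the third row the stated split gives the right answer and the by-arm table dilutes it.

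**The case against.** The strongest case on the other side has four parts.

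**By-arm reporting is not excluded.** A reader might infer that adverse events will not be shown by randomised arm at all, and that no randomised safety comparison remains. The text does not say so. A sub-group display can sit beneath a by-arm report, the full protocol is available on request, and table layout is often settled there. This stands. What remains is that the article does commit to one grouping, immediately after stating the as-randomised principle, and a person following it as written would produce the mixed table.

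**The rule does not always conceal harm.** A reader might infer that it systematically hides harm. The third row of the table shows otherwise. The deterioration that triggers a withdrawal also happens while the patient is still receiving therapy and is counted there; only later events move. This stands, and it limits the point to delayed and post-withdrawal events.

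**Other safety information is analysed as randomised.** It would go too far to call this table the trial's main safety evidence. Hospital admissions, length of stay and readmissions, observer-rated and self-rated depression, and psychological distress are all listed clinical outcomes, and outcomes are compared between the arms. Although there is no data monitoring committee, serious events go to the sponsor, an independent panel monitors conduct, and the study can be halted. This stands too.

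**A split by receipt may be meant for the deferred course.** If recording continues while the wait-list arm later receives therapy, a display by receipt is sensible for that period. It does not justify the split during follow-up, because that therapy comes after the 6-month assessment.

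**Conclusion.** The point holds in a limited form. The article's only stated grouping for adverse events departs from the as-randomised principle in the preceding sentence. On the trial's own schedule, more than half of the not-receiving category (56% to 57% with no attrition, 58% to 60% if 30% to 50% stop therapy at week 7) is intervention-arm time. Events that come late or after withdrawal would be pooled with wait-list events.

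The effect on an apparent contrast depends on when the events occur: 1.28 in place of 2.0, 0.64 in place of 1.65, or an undistorted 2.0 where the by-arm figure is 1.35. Those ratios rest on assumed event rates. The person-time shares rest on the article's schedule, a 24- to 26-week reading of 6 months, complete follow-up and, for the upper range, the assumed withdrawal pattern.

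Severity is moderate. This is a descriptive feasibility study of 30 participants with no planned test on adverse events, and its hospitalisation and symptom comparisons are unaffected. Dated events with known allocation can be retabulated at any time.

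**What to change.** Replace the adverse-event sentence under Clinical outcomes with one that:

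- reports adverse and serious adverse events by randomised arm over the whole follow-up to 6 months after the course, giving patients with an event, number of events and person-time;
- keeps the receiving/not-receiving split as a supplementary display within arm, with the intervention arm divided into during the course, after withdrawal from therapy, and after the end of the course, and with a definition of when a participant counts as receiving;
- shows any events recorded during the deferred wait-list course separately.

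The supplementary display is worth keeping because it shows an excess confined to the course, which the by-arm table dilutes. The cost is one sentence and a slightly longer table. No new patients or assessments are needed, and the event and withdrawal dates required are those the current rule already depends on.
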